#### Screening

As part of routine clinical care, PWH undergo tablet-based, PRO screening with the AUDIT-C approximately every six months. Based on validated cut-points (AUDIT-C scores ≥ 3 for women or ≥ 4 for men), administration of the 10-item AUDIT will be triggered in the PROs. Women with AUDIT scores ≥ 5 and men ≥ 6 then receive the MINI International Neuropsychiatric Interview alcohol domain (MINI) [38] to assess for AUD. When a patient screens positive for UAU, a staff member designated by the site will receive an automated alert via pager with the recommended intervention based on UAU severity. The patient is then approached, consented, and linked to an EBI if they are interested. This system has been programmed into the CNICS PRO platform from earlier work [22].

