*Stepped care procedure*: For PWH with UAU without moderate to severe AUD based on screening, CBI Prime will be delivered by computer or person based on clinic site or patient preference. For those with moderate to severe AUD, PWH will receive CBI Problem (computer or person delivered) tailored to higher alcohol use severity that includes information on pharmacotherapy. In addition, they are provided with three options: CBT4CBT, alcohol pharmacotherapy, or both. At their next scheduled clinic visit (within ~ 4–6 months), PWH will undergo the PRO, and they will receive a second intervention based on this follow-up AUDIT-C score. PWH who continue to drink at unhealthy levels will be stepped up to a higher level of care and receive CBI Problem that reinforces alcohol pharmacotherapy and addresses medication adherence barriers. They will also be offered CBT4CBT and alcohol pharmacotherapy (see Fig. 2). Those with alcohol below unhealthy levels receive a brief intervention with affirming messages via CBI Prize.

As part of the design of the trial, clinics can choose to offer flexible options for the delivery of alcohol EBIs including CBI, face-to-face with a provider, or telemedicine. These modalities will vary both within and between clinics dependent on clinic and patient preferences and capacity. A staff member selected by each site, who could be a social worker, behavioral health specialist, or another appropriate professional depending on the clinic’s structure and staff availability, will facilitate interventions. Clinic operations will be pragmatic, and thus, it is possible staff will turn over during the study period. During the practice facilitation period, the practice facilitator will be available to support sites through any barriers that arise, including staff turnover.

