##### Study outcomes

Our study outcomes, guided by RE-AIM, are described in Table 3 below.

**Table 3 Tab3:** Study outcomes using the RE-AIM framework

Dimension	Exemplar Use Defined by NCI	Present Study Measure
**R**each	• Percent of individuals who participate, among all patients	Percent of patients with UAU who receive an alcohol EBI
	• Characteristics of participants compared to non-participants or to target population	Above measure compared across racial/ethnic groups, gender, and clinical characteristics
**E**ffectiveness	• Measure of primary or broader outcomes	1) Reduced UAU (AUDIT-C score < 3/4 women/men)* 2) Viral suppression (HIV-RNA < 200) 3) ART adherence (> 90%) 4) PEth
**A**doption	• Use of qualitative methods to understand adoption at setting level • Use of qualitative methods to understand staff participation	Barriers and facilitators to delivering alcohol EBIs, intervention components important to enhancing delivery and site preferences related to selection of computer or person delivered intervention.
	• Percent of staff invited that participate	1) Provider report of delivering alcohol EBIs 2) Percent of providers prescribing AUD pharmacotherapy among all clinic providers
**I**mplementation	• Percent of intervention delivery or calls completed, etc. (e.g., adherence or consistency)	1) Percent of patients reporting receiving an alcohol intervention since their last visit among all responding to the PROs 2) Percent of alcohol treatment sessions completed
**M**aintenance	• Measure of primary outcome (with or without comparison to a public health goal) at ≥6mo follow-up after final intervention contact	Percent of patients reporting receiving an alcohol intervention in the past six months among all responding to PROs at six months post final contact with Practice Coach

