## Reach and effectiveness evaluation (clinical measures of UAU and HIV care, Aim 2b)

Reach and Effectiveness will be assessed using an interrupted time series with synthetic control to evaluate whether practice facilitation is associated with our primary implementation outcome (percent of patients reporting receiving an alcohol intervention since their last visit among all responding to PROS across all CNICS sites) and with our secondary effectiveness outcomes (alcohol use, ART adherence, and viral suppression) [67, 68].

An interrupted time series design allows for conducting a rigorous naturalistic study, results can be displayed graphically to intuitively represent findings, historical trend is accounted for in the analytic model, and the size of the effect can be estimated at different times post intervention dissemination [69–71]. Addition of synthetic control can improve estimation of the counterfactual condition in which the intervention was not added to the specific HIV clinics by reducing selection bias and satisfying the parallel trends assumption, which is needed for controlled interrupted time series analyses [69].

The sample will include all patients with UAU seen at each of the CNICS sites during the study. The CNICS sites that did not have the intervention will be the control sites for the interrupted time series with synthetic control. The outcomes will be expressed as a proportion per month. Therefore, the denominator for all outcomes is all patients with UAU with a visit to the participating CNICS clinics for each month of the study period. Numerators for the effectiveness outcomes are defined as follows: (1) Implementation based on patient report (primary outcome); (2) AUDIT-C score ≤ 3 women and ≤ 4 men; (3) viral suppression as indicated by HIV RNA ≤ 200 copies; and (4) high adherence to ART defined as 90% on the visual analog scale.

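### The monthly denominator of patients with UAU has no time anchor; if UAU is judged at that month's visit, the alcohol outcome cannot show response and responders leave the series

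*Protocol article*

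**What the plan says.** The Aim 2b section (Reach and effectiveness evaluation) describes the sample as follows: "The sample will include all patients with UAU seen at each of the CNICS sites during the study". It expresses outcomes as monthly proportions and then states that the "denominator for all outcomes is all patients with UAU with a visit" to a participating clinic, month by month. Neither sentence says at which screen UAU is judged.

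Other places in the article that bear on this:

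- **Screening.** A positive screen is "AUDIT-C scores ≥ 3 for women or ≥ 4 for men". Screening repeats: "PWH undergo tablet-based, PRO screening with the AUDIT-C approximately every six months".
- **Alcohol outcome.** Table 3 gives "Reduced UAU (AUDIT-C score < 3/4 women/men"). The Aim 2b numerator list gives "AUDIT-C score ≤ 3 women and ≤ 4 men".
- **Follow-up.** The stepped care procedure plans for patients who improve by the next visit: "Those with alcohol below unhealthy levels receive a brief intervention with affirming messages via CBI Prize".
- **Receipt of an intervention (primary outcome).** The opening paragraph of Aim 2b and the Implementation row of Table 3 both take everyone who answers the PROs as the denominator. Later in Aim 2b the same outcome is listed first among the numerators that go with the UAU-only denominator. The Reach row of Table 3 is a separate measure, and that one is confined to patients with UAU.

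**The concern.** UAU is both the condition for entering the denominator and, when it resolves, the event counted in the numerator. If both are read from the same visit, one excludes the other.

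The problem spreads beyond the alcohol outcome. The receipt question looks back to the previous visit, so a patient treated at visit 1 can report it only at a later visit. If that patient has improved by then and UAU is judged on the current score, the patient is no longer counted. The series for receipt, adherence and viral suppression would then describe mainly those in whom treatment did not work. The synthetic control does not remove this, because the extra exits would be caused by the intervention, at intervention sites, after roll-out.

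At stake are the secondary alcohol outcome as a whole and, if the UAU-only denominator governs it, the primary outcome.

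**Working it through.** The plan prints no figure for this point, so there is none to reproduce. Step 1 uses only the article's cut-points and the fact that AUDIT-C scores are whole numbers. Steps 2 to 4 are illustrations with assumed rates.

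**1. Overlap of denominator and numerator when UAU is judged at the same visit**

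| | Denominator | Table 3 numerator | Overlap | Aim 2b numerator | Overlap |
|---|---|---|---|---|---|
| Women | 3 or more | below 3 | none | 3 or below | score 3 only |
| Men | 4 or more | below 4 | none | 4 or below | score 4 only |

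The Table 3 version is therefore 0% in every month at every site. The Aim 2b version is the share of positive screens lying exactly on the threshold.

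**2. Does the Aim 2b version track response?** Assume men with baseline scores 4 to 12 whose frequencies decline geometrically with ratio q, a share r who fall below 4 by the next screen, and non-responders who keep their score.

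- Same-visit denominator: the share at score 4 among those still positive is (1 − q)/(1 − q⁹). For q = 0.65 this is 0.35/0.979 = 36%. For q = 0.75 it is 0.25/0.925 = 27%. Neither depends on r, while a share r of the index patients (20%, 30% or 40%) leaves the series.
- Earlier-screen denominator with the below-4 numerator: the result is r itself, so 20%, 30% or 40%.
- Earlier-screen denominator with the 4-or-below numerator (q = 0.65): about 49% when r = 20% and 61% when r = 40%. The level is inflated by patients who still screen positive, and a 20-point gain shrinks to about 12 or 13 points.

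**3. Receipt of an intervention under a same-visit UAU denominator.** Assume 60% of index patients received one, and 20% of the untreated respond.

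- 40% of the treated respond: 0.60 × 0.60 / (0.60 × 0.60 + 0.40 × 0.80) = 0.36/0.68 = 52.9%.
- 50% of the treated respond: 0.60 × 0.50 / (0.30 + 0.32) = 0.30/0.62 = 48.4%.
- Equal response in both groups: 60%, no distortion.

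On this reading, the better the intervention works, the lower its recorded delivery.

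**4. Viral suppression.** Assume 90% suppression in responders and 75% in non-responders, with response rising from 20% to 40%.

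- Earlier-screen denominator: 0.2 × 0.90 + 0.8 × 0.75 = 78%, rising to 0.4 × 0.90 + 0.6 × 0.75 = 81%.
- Same-visit denominator: 75% before and after.

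**5. The readings that the wording allows**

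| UAU judged | Responders | Alcohol outcome |
|---|---|---|
| At the month's visit | leave | 0% (Table 3) or threshold scores only (Aim 2b) |
| At any time in the study | stay | membership depends on later screens; low scores before a first positive screen count as reduced UAU |
| At an earlier screen | stay | works with the Table 3 cut-points |

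**The case against.** The strongest reply is that the third reading is the intended one. Table 3 speaks of a reduction, which presupposes earlier UAU, and Table 2 and the stepped care procedure follow patients from a positive visit 1 to a visit 2 at which some have improved. A full protocol or analysis plan that is not shown may hold the index rule. This stands as a reason not to say that the outcome is certainly empty. It does not clear the text, which ties the denominator to visits in each month and never mentions an earlier screen.

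Four further points limit what can be claimed:

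- A reader might infer that responders are lost on every reading. They are not: under UAU at any time in the study they stay in, and the fault there is the different one shown in step 5.
- A reader might infer that the outcome is 0% as the analysis section prints it. The zero needs the Table 3 cut-points; the Aim 2b cut-points give a non-zero but uninformative figure.
- A reader might infer that the primary outcome is biased as defined. If the definition among all PRO responders governs, nobody leaves when the AUDIT-C falls. The bias follows only if the later UAU-only sentence overrides it, and the article does not say which prevails.
- A reader might infer that a UAU patient with no viral load or PRO in the month is scored as a failure. The article does not say so, and the handling of missing values commonly sits in the analysis plan.

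Lastly, a remedy keyed only to the most recent PRO would bring the loss back: a patient negative at visit 2 would drop out at visit 3.

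**Conclusion.** The concern holds in conditional form. The stated denominator does not fix when UAU is judged. Read as UAU at the month's visit, it makes the alcohol outcome 0% or a count of threshold scores, and it selects non-responders for the other series. Read as UAU at any time in the study, it conditions on the future. Only the earlier-screen reading gives a usable outcome, and the text does not select it.

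Two contradictions remain on any reading: the alcohol cut-points differ between Table 3 and Aim 2b, and the primary outcome has two denominators.

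The overlap result rests on the article's own cut-points. The percentages in steps 2 to 4 rest on assumed response, receipt and suppression rates; they show direction and plausible order of size, not what this trial will observe. This is more than missing detail, because a stated rule fails on a natural reading and conflicts with the primary outcome's own definition. It should be settled before the series are built.

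**What to change.** 1. Define cohort membership by a positive UAU screen before the current visit: either an index screen, or any positive screen within a fixed look-back. With PROs about six months apart, a look-back longer than two intervals (2 × 6 = 12 months) is needed so that one negative follow-up screen does not remove a responder.
2. Keep members in the denominator whatever their current AUDIT-C.
3. Apply the same rule at intervention and control sites, before and after roll-out, so that falls in score that would happen anyway are matched.
4. Align the alcohol numerator with the screening cut-points (below 3 for women, below 4 for men) in both Table 3 and Aim 2b.
5. State one denominator for the primary receipt outcome: all PRO responders or the UAU cohort. If both are wanted, name one as primary and report the other separately, for example as Reach.

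The cost is protocol and analysis-plan wording, a different data query, and somewhat smaller monthly counts because each patient needs an earlier PRO. No new data collection is required.

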### Implementation strategy: practice facilitation

In this Hybrid Type 3 implementation-effectiveness study [45], we are testing practice facilitation as the implementation strategy. Practice facilitation uses multiple discrete implementation strategies supported by a practice coach (internal or external) who offers flexible supports throughout the implementation period that are tailored to local context (e.g., to each site) [46, 47]. The primary objective of practice facilitation is to foster internal capacity for change within a clinical setting. In practice facilitation, practice coaches assist clinical teams in identifying gaps in care and facilitate the team’s development of a plan to address those gaps. This often involves activities of education or knowledge brokering, technical assistance, coaching, expert consultation, and other supports as identified by the local site [48].

For this study, we are providing the three clinics with an external Practice Coach, a person outside of their organization who has expertise in alcohol-related care, practice improvement approaches, and implementation science. The same practice coach will work with each site. In addition, sites will assemble a Local Implementation Team (LIT), an interdisciplinary group of local clinical and administrative champions with the shared goal of implementing the clinical intervention. While each LIT will be expected to have a combination of clinical and administrative research champions, the specific membership of and communication pathways used with each LIT may vary based on the local context of each site.

Practice facilitation will be delivered to each clinic over an 18-month implementation period. The implementation period is organized around three phases of implementation: *pre-implementation*, *implementation*, and *sustainment*. The Practice Coach and LIT will collaborate on implementation activities via regular teleconference meetings and ad hoc activities as described in Table 1, however activities will vary based on each site’s needs, preferences, and infrastructures. To promote continuous learning and adaptation by the implementation team, each clinic’s implementation period is staggered across the study so that their *pre-implementation* phases begin approximately one year apart from one another.

**Table 1 Tab1:** Implementation and practice facilitation activities over the implementation period

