Implementation Phase	Implementation Objectives	Anticipated Practice Coach Activities
*Pre-implementation* (3 months)	• Adapt workflows and/or clinic resources to accommodate delivery of stepped care for UAU • Train & prepare staff on clinical delivery of stepped care for UAU	• Facilitation of bi-weekly meetings with LIT • Identification and preparation of local champions • Identification, development, and/or delivery of training resources • Facilitation of design session and/or focused meetings to design and/or refine workflows for delivery of stepped care for UAU
*Implementation* (12 months)	• Deliver stepped care for UAU within clinic	• Facilitation of monthly meetings with LIT • Real-time delivery of monitoring and feedback data on implementation progress • Facilitation of process improvement approaches (e.g., Plan, Do, Study, Act (PDSA)) • Technical assistance to design and/or refine implementation support materials (e.g., patient and/or provider-facing materials that support implementation)
*Sustainment* (3 months)	• Establish plan for long-term integration and monitoring of stepped care practices in clinic	• Facilitation of monthly meetings with LIT • Technical assistance to develop sustainment plans that address the person, technical, and leadership resources needed to sustain stepped care long-term

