The analysis will be stratified or adjusted by sex, race, and social determinants of health, including housing and income. Should one of the non-intervention CNICS sites be ineligible as a control (for instance, if it is implementing a different alcohol treatment initiative) and optimal weights for synthetic control cannot be determined, we will transition to a comparative interrupted time series. The sequential roll-out of the intervention offers added resilience against temporal secular trend threats. However, we will also model each site as a main effect prior to the intervention, as well as the main effect of time prior to the intervention, and the interaction between time and the intervention. This approach allows each site to have its own pre- and post-intervention slopes relative to its comparative synthetic control, thereby accounting for potential differences between the first, second, and third sites that could arise from secular time trends. To account for potential improvement in the practice coach’s skill over the sequential roll-out, we will also conduct the interrupted time series compared to synthetic control by site to assess for effect heterogeneity. This will be an exploratory analysis as this was not a part of our initial protocol.

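### One post-intervention slope per site combines coached and post-coach months, and under a common study end the mix differs by site, so the by-site check on coach skill can mistake follow-up length for learning

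*Protocol article*

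**What the plan says.** **Timing of the strategy.** Under Implementation strategy: practice facilitation, the protocol article says "Practice facilitation will be delivered to each clinic over an 18-month implementation period". Table 1 divides this into 3 months of pre-implementation, 12 of implementation and 3 of sustainment, with the coach still meeting the local team monthly in the last phase. Sites are staggered so that "their *pre-implementation* phases begin approximately one year apart from one another".

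**Outcome after the coach leaves.** Table 3 places Maintenance six months after final contact with the coach. Data collection therefore runs past the end of coaching, and performance after coaching is a RE-AIM dimension of its own.

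**Analysis.** In the Aim 2b section, outcomes are monthly proportions whose denominator is "all patients with UAU with a visit to the participating CNICS clinics for each month of the study period". The model has site, time and a time-by-intervention interaction, and "This approach allows each site to have its own pre- and post-intervention slopes relative to its comparative synthetic control". A by-site version is added, labelled exploratory: "To account for potential improvement in the practice coach’s skill over the sequential roll-out". Power considerations states the detectable effect as a change in trend.

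**Not stated.** The article does not say which phase opens the post-intervention segment or which month is analysed last. It gives no term or cut-off at the end of coaching.

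**The concern.** Facilitation is delivered and then withdrawn. The article fixes the length of delivery, but the described model does not use it: everything after the interruption lies on one line. That line answers a mixture of two questions, namely what happens while the coach is present and what happens after the coach leaves.

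With starts a year apart and one closing date, the first site has the longest stretch without the coach and the third the shortest. Site order is then tied to length of post-coach follow-up. The by-site comparison uses site order to look for improvement in the coach, so the two explanations cannot be separated. A pooled slope can also understate, or even reverse, a real rise that occurred during coaching at the early sites.

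**Working it through.** **1. The plan's own figure.** 3 + 12 + 3 = 18 months, which reproduces the stated facilitation period.

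**2. Post-coach months per site.** Assumptions: pre-implementation starts at months 0, 12 and 24, and one common calendar end E.

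Post-coach months = E − (start + 18).

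E = 48 is site 3's Maintenance point (24 + 18 + 6).

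| Common end E | Site 1 | Site 2 | Site 3 |
|---|---|---|---|
| 42 | 24 | 12 | 0 |
| 48 | 30 | 18 | 6 |
| 54 | 36 | 24 | 12 |

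At E = 48, the share of the post segment without the coach depends on where the interruption is placed:

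- Interruption at pre-implementation start: 30/48 = 62.5%, 18/36 = 50%, 6/24 = 25%.
- Interruption at implementation start (3 months later): 30/45 = 67%, 18/33 = 55%, 6/21 = 29%.

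If each series instead stops six months after its own final contact, the share is 6/24 = 25% at every site (6/21 = 29% counted from implementation start). The sites then do not differ.

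**3. What one slope does to identical sites.** This is a noise-free illustration, not a prediction. The effect over control is the same everywhere. It rises linearly to +20 points over the first 12 implementation months and holds to month 15, when the coach leaves. It then either persists or declines linearly to zero over 12 months. A straight line with free level and slope is fitted to each post segment, starting at implementation.

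Slope = Σ(m − m̄)e / Σ(m − m̄)², where m is months since implementation start and e the effect.

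- Coached months only (m = 1 to 15): 403.3/280 = 1.44 points per month at every site.
- E = 48, gain persists:
  - Site 1 (45 months): 2053.3/7590 = 0.27
  - Site 2 (33 months): 1393.3/2992 = 0.47
  - Site 3 (21 months): 733.3/770 = 0.95

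| Course after coaching | E | Site 1 | Site 2 | Site 3 |
|---|---|---|---|---|
| Persists | 42 | 0.35 | 0.65 | 1.44 |
| Persists | 48 | 0.27 | 0.47 | 0.95 |
| Decays over 12 months | 42 | −0.39 | −0.09 | 1.44 |
| Decays over 12 months | 48 | −0.38 | −0.35 | 0.57 |

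**4. A second shape.** Let the effect rise 1 unit per month over 18 coached months, with 48 pre-intervention months assumed and a segmented fit with level and slope change. For 48, 36 and 24 post months the slope change is 0.30, 0.48 and 0.82 with a plateau, and −0.23, −0.04 and 0.64 with an 18-month decline. It is 1.00 at all sites if the rise continues unchanged.

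**5. Mean gain instead of slope.** Using the shape in step 3 with persistence and E = 48, the mean effect is 790/45 = 17.6, 550/33 = 16.7 and 310/21 = 14.8 points for sites 1, 2 and 3. This is the reverse order. At E = 42 it is 17.2, 15.9 and 12.7.

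**6. Effect of a change point at coach exit.** In the persistence case, adding a level and slope change after m = 15 returns 1.44 for the coached trend and 0 for the post-coach trend at all three sites, with every month kept.

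**The case against.** **The common end is an inference.** No last month is given, and Maintenance is timed from each site's own final contact. A full analysis plan could close each series that way, and the between-site difference would then disappear. This stands and limits the claim. The wording about each month of the study reads more naturally as one calendar window, though, and the mixing within each site remains under either rule.

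**Post-coach months are legitimate data.** The stated aim of facilitation is internal capacity, and maintenance is one of the outcomes under test. A reader might infer that the main contrast no longer answers whether facilitation increases delivery. The documents do not support that: a lasting effect is a valid target. The fair point is that the model does not distinguish coached from sustained effect, although Table 3 does.

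**The bias is not inevitable.** If improvement continues unchanged after coaching, the slopes agree. Plateau and decay are assumed shapes. However, the outcome is a percentage and cannot rise indefinitely.

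**The direction is not fixed.** A reader might infer that later sites always look better. That holds for slope in the cases shown. For mean gain with persistence, the earlier sites look better.

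**Effects can be estimated at several times.** The article says so as a general feature of the design. With one straight post segment, such estimates all lie on the same line, so this is no safeguard by itself.

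**Recall blurs the boundary.** The primary outcome covers care since the last visit, and patient-reported assessments are about six months apart. Reports made soon after coach exit can describe coached care. This stands and affects how a change point should be fitted.

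**The most exposed analysis is exploratory.** This is correct, and it lowers the severity.

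**Conclusion.** The point holds as a should-fix. As described, the model fits one post-intervention slope per site across coached and post-coach months. It makes no use of the 18-month period that the protocol itself fixes. Under one calendar end at month 48, identical sites with a persisting 20-point gain would show slopes of 0.27, 0.47 and 0.95 points per month, against 1.44 while coached. The exploratory comparison could then credit the coach with learning that did not occur.

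The size rests on four assumptions: exact 12-month staggering, a common end, an interruption at implementation start, and a plateau or decline after coaching. The between-site part fails if each series ends a fixed time after its own final contact.

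Two stronger readings are not supported. One is that the protocol has no stop date for facilitation. It does, at 18 months, and what is absent is its use in the model; the interruption month is equally untied to a phase. The other is a fourfold false learning effect. That ratio (1.44/0.35) needs an end at month 42, which precedes site 3's own Maintenance point.

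**What to change.** 1. State the interruption month relative to the phases in Table 1, and the last analysed month, for each site.
2. Run the by-site comparison of coach skill over the same months since start at every site.
3. Add a change point at final coach contact, with both level and slope free, and report coached and post-coach (Maintenance) trends separately. Keep all months in the model.
4. Because the primary outcome looks back to the last visit, allow a recall lag around the change points, at least as a sensitivity analysis.

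No new data are needed. The cost is one extra segment per site and somewhat less precision for the coached-period trend. Dropping all post-coach months from the main contrast would cost more, since Power considerations ties the effective sample size to the number of time points. It is not proposed here.
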